## Methodology for focus group sessions

Because previous qualitative research has highlighted the stoical nature of people with MPM,^85^ and because it is anticipated that relatives/carers are likely to have had different experiences of MPM and TILT, we will also undertake focus group sessions with participants’ relatives/carers. It is hoped that this will provide additional insight into the overall experience of MPM and participation in a research trial.

When trial participants are invited to join the qualitative interviews, they will also be asked whether they agree to their relative/carer being invited to a focus group session about the research. The participant information sheet for the qualitative research will include information on both the individual participant interviews and the focus group sessions for relatives/carers. If participants agree for their relatives to be approached, they will be asked to provide the name of their relative/carer, and that person will be invited to participate in a forthcoming focus group session. The invitation will be delivered either in person, if the relative/carer has attended the appointment with the participant, or via an invitation letter given to the participant to take home. Participants who do not wish a relative/carer to be invited to a focus group will still be eligible to participate in the one-to-one qualitative interviews.

Focus groups will be separated based on the arm of the trial the participant associated with the relative/carer was in. This is because the experience of relatives/carers will be different depending on which arm of the trial the participant was in. Separating the focus groups will also reduce the risk of distress or conflict arising as result of relatives/carers discovering that different participants were offered different options (see Section 14.4 for further details). Where the number of relatives/carers associated with a particular trial experience is small, e.g. the relatives/carers of participants who were offered bacterial immunotherapy but declined it, individual qualitative interviews will be offered.

Focus groups will be held in a research building on hospital property, separate from clinical care facilities, or in a community building such as a village hall or private room in a pub or café. Because the relatives/carers of people with MPM may be anxious about leaving their relatives alone whilst they participate in the focus groups, every attempt will be made to hold the sessions at the same time and in the same location as an alternate activity for the patient e.g. patient support group or social activity.

Focus groups will be facilitated by [name], with an administrator present to document the first comments made by each participant so they can be identified on the audio-recording later, and to take notes throughout the focus group session.

The topic guide for the focus groups will be designed by the research team, and reviewed and refined in collaboration with patient and public involvement. Attendees will initially be invited to share their experiences of having a relative participate in TILT. They will be encouraged to discuss any expectations or reservations they had prior to the research, and whether the reality of trial participation matched up to this. In addition, the following topics will be covered during the focus group sessions:

- Do they feel that trial participation was onerous for their relative?
- The TwiC design will be explained. Do they find it acceptable?
- How did they feel about their relative receiving OK432/BCG?
- Would they support their relative to participate in future research, and what factors might affect this?
- If their relative declined any aspect of the trial, how did they feel about it?

Sessions will last approximately 2 hours each. They will be audio-recorded, transcribed and analysed using the methodology outlined in section 10.3.

## Qualitative interviews with bereaved relatives

One of the eligibility criteria for participation in TILT is a predicted survival of greater than 3 months. This is to minimise the number of participants who die before completing trial follow up. However, previous clinical trials in this patient population have shown that the accuracy with which clinicians can predict survival is poor.^97^ Therefore it is possible that some participants may die before the qualitative research takes place.

We wish to give the relatives/carers of participants who died during the course of TILT the opportunity to discuss their experience and for their feelings to be heard. This group of bereaved relatives/carers are likely to have a unique experience of research participation at the end of life. For this reason we will seek ethical approval to write a letter of condolence to the bereaved relative/carer thanking them for their relative’s involvement in the research, and inviting them to take part in a one to one qualitative interview with [name]. If they are interested in taking part in the qualitative interviews they will be asked to contact a member of the research team. If the research team does not hear from the relative/carer, there will be no further attempts to contact them.

If bereaved relatives wish to participate in qualitative interviews, they will be given the choice of where and when the interview is held. This is because they may prefer not to return to the hospital where their relative was treated. Additionally, if they wish to have a friend or family member present during the interview, this will be allowed. It is not anticipated that the interviews will be distressing in themselves, however it is appreciated that this will be a difficult and emotional time for relatives. Therefore, if a relative becomes distressed at any point the interviewer will ask them whether they would like to stop, and will terminate the interview if they say yes. If the relative wishes to continue, then the interviewer will do so but will check again later that they are OK to continue. All relatives who express significant distress during an interview will be offered referral to an NHS clinical psychologist and all participants in the study will be provided with a list of useful further contacts for support.

## Sample size for qualitative research

A sample of 20 TILT participants will be invited to undertake individual qualitative interviews. Participants will be purposively sampled from both arms of the trial, including those who completed follow-up, those who withdrew and those who declined any element of the study.

We anticipate at least 15 participants will accept the invitation to interview. Given the relatively homogeneous characteristics of people with MPM (85% men, 75% over the age of 65, industrial occupations), we anticipate this will be sufficient to achieve thematic saturation and the proposed sample size is in keeping with other successful qualitative studies.^2 98^

Four focus groups of approximately 6 relatives will be held (2 in Bristol and 2 in Oxford), yielding a sample size of at least 20. Given the similarity of experience that will be discussed in the focus groups (i.e. caring for a relative with MPM who has participated in a specific arm of TILT), it is anticipated that this will be sufficient to achieve thematic saturation.^98^

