## Study design

This is a multi-centre feasibility study for a single-blind, randomised, three-armed trial of intra-pleural bacterial immunotherapy in people with mesothelioma, based on the trial within a cohort design.

Patients with mesothelioma will be invited to participate in a longitudinal observational cohort study, consisting of pleural fluid monitoring, patient-reported outcome measurements, chest radiography (CXR) and blood tests (the ASSESS-meso study). Eligible patients will be identified from the cohort and randomly allocated to receive a single dose of either intra-pleural OK432 or intra-pleural BCG, or to remain in the cohort as a control. Identification of eligible participants will continue until 8 participants have been randomly selected to receive OK432 or BCG. Randomisation will be undertaken by a centralised, concealed computerised system with minimisation by tumour sub-type and WHO/ECOG performance status (PS). Participants selected to receive bacterial immunotherapy will receive it via an indwelling pleural catheter (IPC), on an unblinded basis. Participants who decline to receive OK432 or BCG following random selection will continue to undergo observational follow up, and their data will be collected as part of the feasibility outcomes.

Participants who are not selected to receive bacterial immunotherapy will continue longitudinal assessments as part of ASSESS-meso, blinded to the existence of the OK432 and BCG arms. This is consistent with real-life clinical care, wherein patients are told about treatments as and when they are going to receive them.

The primary outcome measure is feasibility. The trial will be deemed feasible if the following criteria are met:

- Recruitment rates to time & target >66%, i.e. 8 participants randomised in 12 month recruitment window, or 12 participants in 18 months.
- Attrition rate of <20% (nb this relates solely to attrition due to loss to follow up or participant withdrawal, it does not include attrition due to participant death)
- Data completeness rates >90%

In addition, data will be collected on specific elements of the TwiC methodology to explore the acceptability of the trial design to participants. These will include:

- Acceptance rates for intra-pleural OK432/BCG following random selection
- Number of control participants who were aware of the intervention arm
- Collection of data on participants who decline any element of the trial

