## Random selection

Participants who meet the eligibility criteria will be identified at scheduled assessment visits during their follow up in ASSESS-meso (TILT screening visit). By capturing data on all potentially eligible participants, the ASSESS-meso database will also function as a screening log, recording data on patients who decline to join TILT, and documenting their reasons for non-participation.

12 eligible participants will be identified and randomly allocated to receive either OK432 or BCG or to remain in ASSESS-meso as a control. Random selection will occur at Week 0. Randomisation will be undertaken by a centralised, concealed, computerised randomisation service, stratified by WHO/ECOG performance status on the day of randomisation, following drainage of (0 vs ≥1) and tumour sub-type (epithelioid/cytological diagnosis versus non-epithelioid). Screening and randomisation are designated ASSESS-meso related activities.

Participants will be unaware that random selection is taking place. Participants who are selected to receive either OK432 or BCG will be informed, provided with a participant information sheet and given time to consider participation, before being invited to join the trial. Participants who are not selected will continue observational follow up in ASSESS-meso. This process is acceptable to ethics committees, as to be eligible for TILT, participants in ASSESS-meso must have already given their consent to undergo randomisation for future trials.

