## Sample size & recruitment targets

The target sample size is 12 participants, of whom 8 will be randomly selected to be offered OK432 or BCG and 4 will continue in ASSESS-meso as controls. This sample size is based on previous feasibility studies in mesothelioma.

It is anticipated that the majority of participants who are offered bacterial immunotherapy will consent to receive it, as the burden of treatment is low (a single dose on one occasion), the treatment intervention is well established in other clinical scenarios and trial follow up assessments are the same as they would be within ASSESS-meso. Non-acceptance of bacterial immunotherapy will be collected as part of the feasibility outcomes for the trial, and qualitative interviews will explore these participants’ reasons for non-acceptance of bacterial immunotherapy.

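### Section 10.6 plans to invite 20 TILT participants and interview at least 15, but the trial randomises only 12, and the focus-group target does not fit the section 10.4 procedure

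*Protocol*

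**What the plan says.** The trial size is fixed in two places. The section on sample size and recruitment targets says "The target sample size is 12 participants, of whom 8 will be randomly selected to be offered OK432 or BCG"; the other 4 people form the control group. The random selection section says "12 eligible participants will be identified and randomly allocated to receive either OK432 or BCG or to remain in ASSESS-meso as a control". The end-of-trial section (9.6) closes the trial 12 weeks after the 12th patient enrols, or 12 weeks after the recruitment window closes, whichever is sooner. The study is described as a "multi-centre feasibility study for a single-blind, randomised, three-armed trial of intra-pleural bacterial immunotherapy", and the flowchart gives 4 people per arm at 1:1:1.

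Section 10.6 sets the qualitative sample: "A sample of 20 TILT participants will be invited to undertake individual qualitative interviews", drawn from both arms and including people who withdrew or declined something. It continues: "We anticipate at least 15 participants will accept the invitation to interview". For relatives: "Four focus groups of approximately 6 relatives will be held (2 in Bristol and 2 in Oxford), yielding a sample size of at least 20". It expects thematic saturation from each of these samples.

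Two method sections bear on this. Section 10.3 extends the interview sampling frame to ASSESS-meso members who asked not to be considered for future trials, without giving a number. Section 10.4 asks each participant to name a relative or carer, invites that person, and adds: "Focus groups will be separated based on the arm of the trial". It offers individual interviews where few relatives share a trial experience.

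The plain English summary gives a different trial size: 24 suitable people, 16 of them chosen to receive an agent.

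**The concern.** A sample of 20 cannot be drawn from 12 people, and 15 interviews also exceed everyone the trial will randomise. The relatives' target has the same problem once the one-relative procedure and the separation by arm are applied.

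Acceptability to patients and relatives is one half of the research question in the aims section, and the qualitative work is a main route to answering it. As the numbers stand, the trial could recruit perfectly and still report a shortfall against its stated qualitative sample. The saturation statement would also be citing numbers that the trial cannot supply from its own participants. The three numerical feasibility thresholds (recruitment, attrition, data completeness) do not depend on these figures.

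**Working it through.** This is a counting check; no power formula applies.

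**Inputs.** Randomised: 12, being 8 offered an agent and 4 controls (sections 6.4 and 6.6). Arms: 3, with 4 in each (flowchart). Invitations 20, interviews at least 15, four groups of about 6, relatives at least 20 (section 10.6). Named relatives per participant: 1 (section 10.4).

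**The plan's own figures, taken alone.**
- Implied uptake: 15 / 20 = 75%.
- Focus groups: 4 × 6 = 24, so at least 20 relatives is internally consistent (20 / 4 = 5 per group).

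These internal sums are sound. The population behind them is too small.

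**Interviews against the trial size.**
- Invitations: 20 / 12 = 1.67, or 167% of those randomised.
- Interviews: 15 / 12 = 1.25, or 125% of those randomised.
- Attainable at the plan's uptake: 12 × 0.75 = 9, before deaths.
- Illustration only: if 10% to 30% of participants were unavailable (an assumed range; the protocol gives no rate), 12 × 0.9 × 0.75 = 8.1 and 12 × 0.7 × 0.75 = 6.3, so about 6 to 8 interviews.

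**Relatives against the trial size.**
- Needed for 20: 20 / 12 = 1.67 per participant.
- Needed for 24: 24 / 12 = 2.0 per participant.
- Available with one named relative each: 12 × 1 = 12 in total, 4 × 1 = 4 per arm.
- A group of 6 from one arm: 6 / 4 = 1.5 relatives per participant, all attending.
- If the arms are read as intervention versus control: 8 relatives on the intervention side fill one group of 6 but not two, and 4 on the control side fill none. That is one full group against four planned.

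**How many outsiders would close the interview gap.**
- To reach 20 invitations: 20 − 12 = 8 ASSESS-meso members outside the randomised 12.
- To reach 15 interviews: 15 − 12 = 3 if all 12 accept, or 15 − 9 = 6 at 75% uptake.

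**Check against the size in the plain English summary (24).** Invitations 20 / 24 = 83%; interviews 15 / 24 = 63%; relatives 20 / 24 = 0.83 per participant; 24 / 3 = 8 per arm. Section 10.6 is attainable at that size. This suggests that it was written for a larger trial, which is an inference and not something the protocol states.

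**The case against.** The core count has no rebuttal: no other section corrects it, and it does not come from missing or blacked-out text. The fair objections concern how far it reaches.

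- **Total interviews.** A reader might infer that 15 interviews are impossible altogether. Section 10.3 admits ASSESS-meso members who declined future trials, with no cap, so a total of 15 could be reached with their help. This stands, but section 10.6 says TILT participants, gives no number for the others, and people who refused future trials cannot describe being in TILT.
- **A ceiling of 8.** The consent section counts as TILT participants only those who sign TILT consent, which might suggest at most 8. Section 10.6 itself samples people who declined, so it uses the term more loosely. Twelve is the fair ceiling.
- **Relatives.** The singular wording in section 10.4 suggests one relative each but sets no explicit limit, so 20 is out of reach only under that procedure. The individual interviews offered there, and the separate interviews with bereaved relatives, partly cover small numbers. Neither produces four groups of 6.
- **Both arms.** The protocol sometimes treats the two agents as one intervention side, so the phrase may mean intervention versus control. It is ambiguous rather than plainly wrong.
- **Acceptability.** Acceptance rates, control-arm awareness and data on decliners also inform it, so the answer does not rest on this sample alone.

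**Conclusion.** Wrong as written, and worth correcting. The stated 20 invitations and 15 interviews cannot be met from 12 randomised participants; this needs no assumption. About 9 interviews is the attainable figure if all 12 are invited and the implied 75% uptake holds, and deaths would lower it. The target of at least 20 relatives, in groups of about 6 separated by arm, is not attainable if each participant names one relative.

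The stated numerical basis for saturation is therefore unsupported. A reader might go further and conclude that saturation will not be reached. The protocol does not show that: it argues from a homogeneous population, and nothing in it establishes that 9 to 12 interviews would be too few. Nor does it support a precise figure for interviews lost to death. Its median survival runs from diagnosis, whereas participants enter later and are selected for a predicted survival of at least 12 weeks.

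**What to change.** Reconcile the plain English summary (24 people, 16 chosen), the sample size section (12 and 8), and sections 10.3, 10.4 and 10.6. In section 10.6:

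- Invite all 12 randomised participants, and state about 9 expected interviews at 75% uptake, fewer if participants die.
- State separately how many ASSESS-meso members who declined future trials will be interviewed, and report them apart from trial participants.
- Set the relatives' target at no more than about 12, and use the individual interviews that section 10.4 already allows where an arm cannot fill a group.
- Align the reference to both arms with the three-arm design, or define it as intervention versus control.
- Re-justify saturation at the attainable numbers, or drop the claim.

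The change is to protocol wording. Its cost is that the stated qualitative sample becomes smaller.

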# PARTICIPANT WITHDRAWAL/NON-CONSENT

All participants will have provided written informed consent to trial follow-up, and to sample collection, storage and analysis where appropriate. Participants have the right to withdraw consent at any point. Withdrawal does not have to be justified and will not affect future or on-going care. In the event of withdrawal, any details available for the reason(s) should be recorded in the patient’s eCRF, and clarification on the nature of the withdrawal of consent, as outlined below, should be sought. Patients may still be classified as ‘alive’ or ‘dead’ at the end of their follow-up period, unless consent for clinical data use is withdrawn.

## Withdrawal of consent to all trial involvement

The participant withdraws consent for all trial involvement, including further data collection, sample storage and analysis, and the use of data already collected in the final trial analysis. Samples already taken and follow-up data should be destroyed as per local policy.

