## Withdrawal of consent for further data collection and use of existing data

The participant withdraws consent to further follow-up visits, recording of clinical data and the use of any clinical data already collected. They maintain consent for blood and fluid samples already taken to be analysed.

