# ADVERSE EVENT MONITORING

## Definitions

*Adverse Event (AE)*

Adverse Events (AEs) are any untoward medical occurrence in a patient or clinical trial subject administered an investigational medicinal product (IMP), medical device or intervention and which does not necessarily have a causal relationship with this treatment. This includes any unfavourable and unintended signs, including abnormal laboratory results, symptoms or a disease temporarily associated with an investigational product.

AE must always be recorded on an eCRF and in the patient's medical notes.

*Adverse Reaction (AR)*

Adverse Reactions (ARs) are adverse events where there is evidence to suggest there is a causal relationship between the event and the IMP.

*Serious Adverse Event (SAE) or Serious Adverse Reaction (SAR)*

Serious Adverse Events (SAEs) are defined as any untoward medical occurrence(s) that results in:

- death
- real and immediate threat to life
- hospitalisation
- prolongation of existing hospitalisation
- persistent or significant disability or incapacity
- a congenital anomaly or birth defect
- other health event which in the opinion of the clinician is serious

*Serious Adverse Reaction (SAR)*

Any SAE that is classed as serious in nature and which is consistent with the information about the IMP set out in the summary of product characteristics (SmPC) for that product or listed as an expected reaction in the trial protocol.

*Suspected Unexpected Serious Adverse Reaction (SUSAR)*

Any SAE/SAR that is suspected to be caused by the IMP, but which is not consistent with the information available about the IMP set out in the SmPC for that product or listed as an expected reaction in the trial protocol. If the event is not listed as expected, or has occurred in a more serious form than anticipated, it should be considered a SUSAR.

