## Follow-up after adverse events

Participants experiencing SAEs or AEs will receive the appropriate medical treatment as per standard care. SAE/SAR/SUSAR should be followed up until resolution, including follow-up in ASSESS-meso if the event continues after the end of TILT. After recovery or once the event is considered stable, participants will be followed up in the normal trial or study schedule.

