## OK432

OK432, as used in the context proposed in this trial, is regarded as an IMP and the appropriate approval will be sought from the MHRA and HRA. .

Intra-pleural OK432 is an established treatment for malignant pleural effusions in Japan, South Korea and Taiwan. Since its launch in 1975 adverse event reporting has revealed no significant adverse reactions greater than grade 2 severity. Safety data of intra-pleural OK432 in people with MPM will be collected throughout TILT. Participants who are offered OK432 will be made aware of OK432’s unlicensed status in the UK, and will be asked to provide consent to receive an IMP.

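### Withdrawal options 11.1 and 11.3 make no exception for safety records already made on people given OK432 or BCG, so a reaction can drop out of the by-arm summary of a four-person arm

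*Protocol*

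**What the plan says.** Section 11 of the Protocol sets out several kinds of withdrawal, and two of them reach back to data already held.

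- **11.1 (all trial involvement)** withdraws, among other things, "the use of data already collected in the final trial analysis". It continues: "Samples already taken and follow-up data should be destroyed as per local policy".
- **11.3 (further collection and existing data)** withdraws further visits, "recording of clinical data and the use of any clinical data already collected". Analysis of samples may continue, and destruction of data is not mentioned.
- **The introduction to section 11** allows a participant to be classed as alive or dead at the end of follow-up "unless consent for clinical data use is withdrawn".

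None of these separates safety or dosing records from other data, or people who have been dosed from people who have not. Section 11.2, by contrast, keeps what has already been collected.

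Other sections depend on those records:

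- Section 12.1: "AE must always be recorded on an eCRF".
- Section 12.2 requires all adverse reactions, including expected ones, on eCRFs, because neither agent has been used in this context in this country and this is a feasibility trial.
- Section 12.6: "SAE/SAR/SUSAR should be followed up until resolution".
- Section 14.2: "Safety data of intra-pleural OK432 in people with MPM will be collected throughout TILT".
- The Study design section of the Trial Overview lists adverse events as a secondary outcome.
- Section 13.3 summarises secondary outcomes by randomised arm.

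**The concern.** Someone who reacts badly after dosing may be more likely than others to leave. If that person chooses 11.1 or 11.3, the reaction leaves the analysed data with them. The loss would then depend on the outcome being measured, and the remaining data would make the agent look better tolerated than it was.

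The arms are very small, and the Abstract says that the full-scale trial may carry forward one or both agents depending on these results. One missing reactor could therefore change how an agent appears at that decision. Destruction under 11.1 also cannot be reversed if the question comes up later.

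**Working it through.** **Inputs**

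- Sample size 12, of whom 8 are to be offered OK432 or BCG and 4 are controls (Sample size & recruitment targets).
- Allocation 1:1:1, with N=4 shown for each arm (Trial flowchart).
- Attrition criterion below 20%, counting withdrawal and loss to follow-up but not death (Study design; 9.2).

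**Step 1: the plan's own figure.** 12 × 1/3 = 4 per arm, which agrees with the flowchart. There is no power calculation to reproduce; the sample size rests on earlier feasibility studies.

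**Step 2: weight of one participant.** 1/4 = 25% of an arm; 1/8 = 12.5% of everyone allocated to an agent. If fewer than four in an arm accept treatment, each dosed person weighs more (1/3 = 33% if three accept).

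**Step 3: effect on the reported proportion.** Suppose one person in an arm reacts and all four were dosed. Intervals are exact (Clopper–Pearson) 95%.

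| Records | One arm | Both agents together |
|---|---|---|
| Kept | 1/4 = 25% (0.6% to 80.6%) | 1/8 = 12.5% (0.3% to 52.7%) |
| Removed | 0/3 = 0% (0% to 70.8%) | 0/7 = 0% (0% to 41.0%) |

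The upper limit falls although there are fewer data, because the person removed was the one with the event.

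**Step 4: would the attrition criterion notice?** With all 12 randomised as denominator, 1/12 = 8.3% and 2/12 = 16.7% pass; 3/12 = 25% is the first failure. The protocol does not state the denominator. If only the 8 allocated to an agent counted, 1/8 = 12.5% would pass and 2/8 = 25% would fail. One erased reactor passes either way.

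**Step 5: which records survive?**

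| Record | After an 11.1 or 11.3 request |
|---|---|
| SAE or SAR form sent to the coordinating centre and sponsor within 24 hours (12.5) | Not recalled by section 11 |
| SUSAR report to the REC and MHRA (12.5) | Not recalled |
| Steering committee review of SAE, SAR and SUSAR (16.4) | Not recalled |
| Medical notes (12.1, 12.5) | Not mentioned in section 11 |
| eCRF entries | No exception: use withdrawn under both options; under 11.1, follow-up data also destroyed |

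Under 12.5, non-serious reactions need not be reported to the coordinating centre. They go in the notes, on the eCRF and on a per-participant log, so the gap is widest for them.

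**The case against.** The strongest reply is that little is really lost, and only at the participant's own request. Much of this stands.

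- **Serious events remain visible.** A reader might infer that a severe reaction would be deleted outright, or hidden from the steering committee. Sections 12.5 and 16.4 do not support that: serious events reach the sponsor promptly, and the committee reviews them all. These routes do not, however, put the event back into the by-arm analysis.
- **Retention is the usual case.** Section 14.7 keeps people who withdraw in follow-up unless they specifically refuse it, section 11 requires the type of withdrawal to be clarified and any available reason recorded, and 11.2 keeps existing data. Loss needs an explicit request under 11.1 or 11.3. That limits how often it happens, not what the rule does when it applies.
- **It is not a flat contradiction.** One might infer that section 11 directly breaches 12.1, 12.6 and 14.2. Those sections govern recording, follow-up and collection, while section 11 governs use and retention after consent is withdrawn. An event can be recorded as required and its use later withdrawn. The sections are unreconciled rather than logically incompatible. The commitment to collect safety data throughout TILT is in 14.2 only; 14.3 instead describes monitoring for disseminated BCG at every visit.
- **Late BCG infection is a separate matter.** Section 7 mentions pleural infection more than six months after delivery. An event first arising after withdrawal would not be captured by keeping earlier records either.
- **Four people cannot bound an event rate in any case.** This is true, as the intervals show. The primary outcome is feasibility, and no tolerability threshold exists for one record to reverse. Section 13.2 also omits adverse events from its list of potential secondary outcomes, although the Study design section includes them.
- **Part of the detail lies elsewhere.** The local destruction policy, data management plan and consent pages are not available. They may soften the effect, but nothing in the protocol text does.

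**Conclusion.** The point holds in a limited form. As written, 11.1 and 11.3 allow adverse event and dosing records of a dosed participant to be removed from the final analysis, and 11.1 also directs that follow-up data be destroyed. This does not fit 12.2, the listing of adverse events as a secondary outcome, or 13.3. The loss falls on the trial dataset and final analysis, and mainly on non-serious reactions.

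One erased reactor in a fully dosed arm moves 1/4 to 0/3 without breaching the attrition criterion. That assumes all four accepted treatment, one reacted, and that person asked for existing data to be withdrawn. The protocol gives no basis for a probability of this. A reader could construct a worse case, with both withdrawals permitted out of 12 falling in one arm; the rules allow it, but nothing in the document suggests it is likely.

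The direction of bias, towards apparent tolerability, depends on withdrawal being related to the reaction. That is plausible but not established. The point merits a correction, at a priority below changes that must be made.

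**What to change.** Amend 11.1 and 11.3 so that, for anyone who has received OK432 or BCG, adverse event, SAE and IMP-administration records made up to the time of withdrawal are retained and included in the safety summary by arm. State the exception in the TILT information sheet and consent form, so that participants know of it before they agree to treatment.

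Leave the other withdrawal options as they are. Retaining all data in every case would abolish consent choices the protocol deliberately offers, and the concern does not require it.

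The cost is a short rewording of section 11 and of the consent documents. Dosed participants would lose the option of having those particular safety records removed. That is a small but real reduction in what they can ask for, and the consent form should say so plainly.
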